[figure not shown]

**Full title**

PROMISE EBF: Promoting Infant Health and Nutrition in Sub-Saharan Africa: Safety and Efficacy of Exclusive Breastfeeding Promotion in the Era of HIV: a multicentre, community-randomised, controlled trial comparing the safety and efficacy of peer-support for exclusive breastfeeding compared to standard care.

## **1.0 Introduction**

The single most effective way of saving the lives of millions of young children in developing countries would be the promotion of exclusive breastfeeding (EBF). Over a period of 10 years it could save the lives of an estimated 15 million children.

*“Infants aged 0-5 months who are not breastfed have seven-fold and five-fold increased risks of death from diarrhoea and pneumonia respectively, compared with infants who are exclusively breastfed. At the same age, non-exclusive rather than exclusive breastfeeding results in more than two-fold increased risks of dying from diarrhoea and pneumonia.”*

This assertion, and related comments and findings, set out by the Bellagio Child Survival Group in a recent article in the Lancet summarising findings from international research of how best to reduce infant mortality in developing countries, is made despite our limited knowledge of how best to promote EBF. This proposal addresses the urgent need to tackle this limitation. How best to promote EBF needs attention because it will be necessary to secure high rates of support for EBF from young mothers, and we do not currently know the best way to bring this about, particularly in the cultural context of Africa. Unless we can find more effective strategies to combat poor feeding practices in both health facility and community settings, the child mortality will continue to be high.

The benefits of breastfeeding and the negative effects of artificial feeding in underprivileged environments were clearly brought to public attention in the 1970'ies, backed by increasingly strong scientific support. As a result the International Code of Marketing of Breast-milk Substitutes and subsequent World Health Assembly Resolutions were created in the 1980'ies to avoid marketing of infant foods, teats and bottles in ways that could interfere with breastfeeding. In the early 1990'ies, UNICEF started the “Baby-friendly Hospital Initiative” (BFHI), which decreased many of the practices in the health care system that had a negative impact on breastfeeding. Together with many of the other child health programmes during these decades these interventions contributed to a reduction in child morbidity and mortality.

### **1.1 Exclusive breastfeeding – an even better version of breastfeeding**

EBF means that the infant receives nothing else than breast milk, not even water. That breastfed

children do not need anything besides breast milk, not even water, and not even in hot climates, was discovered in the 1970s. A decade of research confirmed this, followed by an attempt to define breastfeeding into various patterns by WHO and others. Since then, research has begun to suggest that, even in developed countries, EBF protects against gastrointestinal, respiratory and other infections, and that the protective effect is enhanced with greater exclusivity of the breastfeeding. Exclusivity also increases the duration of amenorrhoea, positive for maternal health and birth spacing.

EBF is not a traditional concept; beliefs and practices regarding a wide range of early supplements are common around the world, and often seem to reflect beliefs expressed by early physicians such as Galen. Nor is it widely understood by health care professionals, given the lack of information on it even in most paediatric basic training.

Thus EBF is not widely practised anywhere except perhaps in much of Scandinavia and parts of some countries in other regions, including a few African countries. The best source of data on the duration of exclusive breastfeeding in developing countries is the Demographic and Health Surveys run by Macro International Inc. and funded by USAID. In only 23% of the 61 national surveys from Sub-Saharan Africa available online:

([http://www.measuredhs.com/statcompiler/table\\_builder.cfm?userid=90787&usertabid=101224](http://www.measuredhs.com/statcompiler/table_builder.cfm?userid=90787&usertabid=101224) )

is the median duration of exclusive breastfeeding longer than one month. Even this overestimates the amount of exclusive breastfeeding being done in Africa, as the indicator used is not “EBF since birth,” but “EBF the day before the survey.”

So if EBF is able to lower child mortality by 13%, why is it not promoted on a large scale already today? Two major reasons are: fear of HIV transmission through breast milk and uncertainty about the micronutrient status in children exclusively breastfed for 6 months.

## **1.2 Breastfeeding and risk of HIV transmission**

When an HIV-positive mother breastfeeds for 1.5 years or more, this appears to lead to an additional 15% risk of postnatal HIV transmission on average. At a population level the epidemiological evidence is that exclusive breastfeeding should still be promoted even in countries with high prevalence of HIV. For many HIV positive mothers the risk of transmitting HIV to their children is outweighed by the risk of the infant dying if not breastfed because of the poor socio-economic and environmental conditions they live in. Limited evidence suggests that for these women and their children EBF is even more important, not just for minimising respiratory and gastrointestinal infections but also perhaps in reducing the risk of HIV transmission. However in reality the HIV epidemic has undermined breastfeeding promotion efforts especially in countries that would benefit the greatest. In addition, expensive approaches of dealing with HIV

have removed the focus from breastfeeding as an inexpensive way of promoting optimal child health.

While the exact mechanism for HIV transmission during breastfeeding is unknown, there are a range of known maternal risk factors including nutritional status, viral loads in plasma and breast milk and CD4 count, breast pathologies, including subclinical mastitis. The longer the breastfeeding lasts, the greater the transmission risk. Oral thrush in the infant may also increase risk of transmission. One study in which infants were exclusively breast-fed for 3 months found that the risk of transmission appeared to be greatly reduced compared with the normative pattern of mixed feeding. On the other hand non-breastfeeding also has a detrimental effect on child survival. Breastfeeding still seems to be a reasonable trade-off for poor African HIV-positive mothers, particularly if exclusive.

Piwoz and Ross estimate that perhaps half of all breastfeeding transmission of HIV may be due to the breast problems mentioned above. Thus lactation management needs to be readily available to assist women to breastfeed properly from the outset and to reduce breast damage when problems do arise.

### **1.3 EBF and micronutrient status**

Exclusively breast-fed babies appear to grow well for up to six months in both developed and developing countries, suggesting that severe deficiency of most micronutrients is unlikely. However, in recently deciding to recommend EBF for six months, WHO warned that, based on one randomised trial in Honduras, infant iron status might not be optimal at six months and that data were inadequate to judge what effect six months of exclusive breastfeeding might have on infant status regarding certain other micronutrients, particularly zinc and vitamin A. That such basic research to establish the “normal” micronutrient status of infants exclusive breast-fed from birth has not been done reflects the fact that almost no researchers have utilised a strict definition of EBF and that very few infants in most countries have been fed that way. The use of a strict definition in doing such research would seem justified, as the gut environment, including its microflora, is likely to influence the absorption of certain micronutrient but also to be influenced by the addition of most types of supplements and even medications such as antibiotics.

### **1.4 The intervention: Peer Counselling**

The constraints discussed above have meant that efforts to promote EBF have been rudimentary so far, consisting mainly of the BFHI. But in Africa nearly all such efforts have come almost to a complete standstill in recent years. EBF promotion therefore needs to be reshaped in this era of HIV. The challenge is urgently to put back on track the promotion of exclusive breastfeeding for

the benefit of the world's children without losing credibility by doing it indiscriminately. PROMISE will to fine-tune and test an upgraded version of EBF-promotion that is HIV-sensitive and to do it in four African countries with a high prevalence of HIV where it is most needed. In particular, it will be the first study to deal explicitly with each of these constraints, opening the way for more widespread and successful promotion of EBF, especially in Africa, ultimately giving back to Africa one of the powerful and cheap interventions to prevent child mortality and morbidity.

Peer counselling is a proven cost-effective approach for changing behaviour, for example, preventing HIV infection. Several studies have also examined its impact on breastfeeding behaviour. Based largely on quasi-experimental studies peer counselling was shown to have an impact on the duration of any breastfeeding. Kristin et al in the USA obtained increases in EBF among women who obtained services from peer counsellors compared to those for whom requested services were not available; Haider et al in Bangladesh in a trial randomised by community and Morrow et al in a trial randomised at individual level in Mexico also obtained substantial increases. However, in the USA two trials failed to have much impact. Green summarised the results of four unpublished quasi-experimental studies. Impacts of peer counselling in intervention compared to comparison/control groups were seen in studies done in Chile and Honduras. In another study in Honduras and one in Mexico, little effect was achieved, presumably due to limited implementation. Thus we feel that peer counselling is promising enough to be chosen as the intervention to focus on but not proven clearly enough (indeed, hardly tested at all in Africa) to prevent it from being ethically randomised.

### **1.5 Potential impact**

This study will provide the first data from a randomised trial on the safety and efficacy of peer counselling as a way of increasing rates of exclusive breastfeeding in the African context. Outcomes include morbidity, growth, and micronutrient status.

The range of four countries included will enhance generalisability of these findings. The study will provide measures of the impact of this intervention on infant morbidity, growth and micronutrient status as well as the costs, efficacy and implications for the health care system of implementing such an intervention. Thus it will in one package provide all the information policy makers need and hopefully will thus lead to more rapid replication if the outcome is positive. Peer counsellors are by definition local women and thus a low-cost intervention suitable to resource-poor environments.

In Europe the health implications of exclusive breastfeeding for six months are not well known, perhaps largely because it has been rare. A relatively long period of EBF has however been the norm in Norway and Sweden for over a decade, and randomised trials comparing various

outcomes for 4 vs. 6 months EBF are ongoing in Sweden and Iceland. Four months of EBF is rare in most of Europe (WHO Global Data Bank on Breastfeeding [http://www.who.int/nut/db\\_bfd.htm](http://www.who.int/nut/db_bfd.htm) ) and yet widely agreed upon to be important for infant health even in Europe. As far as we know, efforts to promote it in Europe have been limited. Thus it is important for European universities to learn how this can be done.

PROMISE will generate cross-fertilization among the three European Universities to learn from and share with each other and the African colleagues several areas of research. None of the partners are experts in all these areas (breastfeeding promotion, micronutrients, HIV). We expect a long-term research consortium to emerge from this beginning.

PROMISE EBF will provide an example to the world of how efforts to promote exclusive breastfeeding and avoid postnatal HIV transmission can be done jointly, and what synergisms may result. Methods employed and costs will be documented and reported on to increase ease of replication and sustainability.

In Africa, there is a growing awareness that strategies must be identified and tested that can lead to the highest possible infant survival in the face of the risk of postnatal HIV transmission. In 1997 UNAIDS, WHO and UNICEF changed their policy on HIV and infant feeding, and issued guidelines for implementing this new policy a year later. Whereas previously countries where most infant mortality was due to infection and malnutrition were advised to promote breastfeeding irrespective of the mother's HIV status, the new policy called for individual counselling on the advantages and disadvantages of breastfeeding vs. artificial feeding that would enable mothers to make an informed choice. UNICEF provided free formula at a number of pilot sites.

Later a World Health Assembly Resolution recommended that replacement feeding be advised where it was acceptable, feasible, affordable, safe and sustainable. In response to concerns that pilot site approaches are being expanded without taking into account the potential importance of exclusive breastfeeding, several UN agencies have endorsed a new "Framework for Priority Actions" for countries that want to go to scale with such approaches.

## **2.0 Objectives**

The objective of this study is to lead the way in the promotion of child health by developing, implementing and assessing the health impact of an intervention to promote exclusive breastfeeding in African settings where a high prevalence of HIV is a barrier.

### **2.1 Primary objectives**

The primary objectives are to assess in a community-randomised trial with intention-to-treat analysis:

1. the impact of peer-counselling in increasing the exclusive breastfeeding rates at 3 months of age and
2. the effects of the trial on infant morbidity (2 weeks diarrhoeal disease point prevalence at 3 months)

### **2.2 Secondary objectives**

The secondary objectives are:

1. To assess the effects of the trial on growth (up to 6 months of age) and micronutrient status
2. To relate infant morbidity, growth, micronutrient status to actual feeding pattern
3. To observe how micronutrient status develops in exclusively breast-fed infants up to six months of age
4. To assess the cost-effectiveness of the interventions in terms of cost per averted child morbidity, and per additional Disability Adjusted Life Year
5. To assess the data collection and handling for field trials using new handheld computer technology
6. To describe the quality, efficiency and equity dimensions of the interventions and to analyse how best to optimise the sustainability of the intervention for the health care sector
7. Transfer of technology and capacity regionally between the African countries, the European countries and between the continents
8. Training of young researchers at the seven partner institutions within their own institution but also through exchange among the partners
9. Building a research consortium that can sustain the collaboration developed in this study

### **3.0 Methodology**

#### **3.1 Design**

A prospective, multi-centre, community-randomised, controlled, experimental design will be used to execute this trial.

#### **3.2 Study settings**

The study will be carried out in four African countries, Burkina Faso in French-speaking West Africa, Uganda in East Africa, Zambia in Central Africa and South Africa in Southern Africa.

In each country one or more districts have been selected as the intervention sites, Banfora in the South-west of Burkina-Faso, Mbale District in Eastern Uganda, Mazabuka in Southern Province in Zambia and three sites in South Africa: Umlazi in Durban, KwaZulu Natal, Rietvlei in Eastern Cape and Paarl in Western Cape. Pregnant women in the randomised communities (=clusters) will be informed about the study and asked if they are willing to participate. If they agree, an enrolment interview will be carried out and based on eligibility criteria the women will or will not be accepted into the study.

#### **3.3 Target population**

The target population will be pregnant mothers who opt to breastfeed their infants who conform to the inclusion and exclusion criteria.

#### **3.4 Inclusion criteria**

The inclusion criteria are:

- Lives in a selected cluster
- Is pregnant  $\geq 6$  months or having given birth less than 7 days ago
- Has no plans to move outside the cluster within 1 year

#### **3.5 Exclusion criteria**

The exclusion criteria are:

- Reduced ability to collaborate for psychological/mental reasons
- Severely ill
- Having given birth more than 7 days ago
- Having given birth less than 7 days ago and it was a multiple birth, or the child has a severe malformation, or death of the mother or the baby.

### 3.6 Randomization

A number of over 30 randomisation units should be identified within reasonable distance from the study office. The randomisation unit varies between sites but will typically be 1-2 villages with an average of 1000 inhabitants (about 35 infants born per year given a birth rate of 3%). Before engaging in the selection of communities, extensive information will be given to community leaders and the rest of the selection process will be done in close collaboration with community leaders. Within the district the suitable communities will be selected and stratified groups considered being similar, based on location, urban-rural, socio-economic status. Care will be taken to allow for 'corridors' between selected communities to be randomised. In each stratum half of the communities will be randomised to intervention and the remainder to control communities. Local community leaders will be further informed about the study.

Each of the clusters should be visited and checked for size, collaborative administrative leaders, not sharing important facilities (water supply, market/shop/trading centre, primary school, mosque, church) with any other potential cluster. If both urban and rural clusters are included no less than 30% of each should be included. The complete list of randomisable clusters will be checked and 24 clusters will be randomised in each site, if applicable in rural/urban strata.

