### 3.7 Sample size and power

Of the primary outcome measures the decrease in diarrhoea is the most difficult to catch. We have based our sample size calculation on the expected reduction in cases of diarrhoea (at the age of 3 months) over the last two weeks of one third from 12% to 8%. With a 95% confidence (alpha error 0.05) and power of 80%, and an average number of infants of 35 per randomised community, and a coefficient of variation between the communities of 0.3, we will need to randomise 48 communities in each arm – a total of 96 communities, see table below.

|                                                                         |    | Increase in EBF from
20 to 40% | Decrease in
diarrhoea |
|-------------------------------------------------------------------------|----|-----------------------------------|--------------------------|
| Proportion in the intervention group                                    | P1 | 0.4                               | 0.08                     |
| Proportion in the control group                                         | P2 | 0.2                               | 0.12                     |
| Percentage point for alfa error = 0.05                                  | z1 | 1.96                              | 1.96                     |
| Percentage point for beta error = 0.20                                  | z2 | 1.28                              | 1.28                     |
| Number of individuals in each community                                 | n  | 35                                | 35                       |
| coefficient of variation of proportions among communities in each group | k  | 0.4                               | 0.3                      |
| Average of P1 and P2                                                    | P  | 0.3                               | 0.1                      |
| Number of communities needed per arm                                    | C  | 12                                | 48                       |

This will include 420 infants in each arm in each country, a total of 840 children per country and all in all 3360 children studied across the four sites. This sample size will very accurately give us the increase in EBF and be able to document the above decrease in diarrhoea morbidity.

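### A community of 1000 at a 3% birth rate has 30 births a year, not 35, and the sample size uses 35 as infants analysed with no allowance for losses

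*Protocol*

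**What the plan says.** Protocol section 3.6 (Randomization) says that the unit varies between sites and is typically one or two villages, with "an average of 1000 inhabitants (about 35 infants born per year given a birth rate of 3" per cent. This is the only place in the protocol where the figure of 35 is derived.

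Section 3.7 (Sample size and power) then assumes "an average number of infants of 35 per randomised community". The driving outcome is diarrhoea at 3 months of age, with an expected reduction "over the last two weeks of one third from 12% to 8" per cent and "a coefficient of variation between the communities of 0.3". The text reads "With a 95% confidence (alpha error 0.05) and power of 80" per cent, and concludes that "we will need to randomise 48 communities in each arm". The same 35 is multiplied out to 420 infants per arm per country, 840 per country, and "all in all 3360 children studied across the four sites".

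In the section 3.7 table, the row "Percentage point for beta error = 0.20" carries the value 1.28.

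Section 3.5 excludes multiple births, severe malformation, severe illness, and maternal or infant death. Section 3.8 expects some mothers to decline and says losses must be kept low. Section 3.7 deducts nothing for any of these.

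**The concern.** The two inputs in section 3.6 do not give the stated result, and the result becomes a design parameter. The number of infants per community enters the cluster formula for both primary outcomes and fixes every enrolment total.

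The parameter also has to mean infants with a 3-month outcome, because the outcome being powered is measured then. Yet 35 exceeds all the births that the described community would have in a year. Even a corrected 30 would be births, not infants enrolled, followed and interviewed at week 12.

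At stake are the support for 3360 and the margin in the diarrhoea calculation.

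**Working it through.** **Inputs (protocol 3.6 and 3.7).** Inhabitants 1000; birth rate 3%; n = 35; 24 communities per site, 96 in all, 48 per arm; p1 = 0.08, p2 = 0.12; k = 0.3; z1 = 1.96; z2 = 1.28 as tabulated. No loss rate is given, so every loss rate below is an assumption.

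**1. The plan's own totals.** 12 × 35 = 420; 24 × 35 = 840; 96 × 35 = 3360. These agree with section 3.7.

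**2. The plan's own number of communities.** The usual unmatched cluster formula with a coefficient of variation is

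C = 1 + (z1 + z2)² × [p1(1−p1)/n + p2(1−p2)/n + k²(p1² + p2²)] / (p1 − p2)²

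At n = 35 the bracket is (0.0736 + 0.1056)/35 + 0.09 × 0.0208 = 0.00512 + 0.001872 = 0.006992. Dividing by 0.0016 gives 4.37. Then C = 1 + 3.24² × 4.37 = 1 + 10.4976 × 4.37 = 46.9, so 47. The plan has 48, which is within one community and equals 4 countries × 12. With z2 = 0.84, the value for 80% power, C = 1 + 2.80² × 4.37 = 35.3, so 36. The plan's 48 is therefore reproduced only with the 90% value.

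**3. Births.** 1000 × 0.03 = 30. To reach 35:
- rate: 35/1000 = 3.5%
- inhabitants: 35/0.03 = 1,167
- time: 12 × 35/30 = 14 months of births

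**4. Total.** 96 × 30 = 2880 per year of births, which is 480 (14%) below 3360. With assumed losses of 10% and 20% this becomes 2592 and 2304.

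**5. Diarrhoea power with 48 per arm.** Power = Φ(√[47 × 0.0016 / bracket] − 1.96).

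| n analysed | Reading | Power |
|---|---|---|
| 35 | as stated | 90.7% |
| 30 | all births, no loss | 87.2% |
| 27 | 10% of 30 lost | 84.4% |
| 24 | 20% of 30 lost | 81.0% |
| 23 | 23% of 30 lost | 79.7% |
| 20 | one third of 30 lost | 75.0% |

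Power crosses 80% between n = 23 and n = 24, at about 22% of 30 births not analysed.

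**6. Communities per arm at n = 30.** The bracket divided by 0.0016 is 4.903.
- z2 = 0.84: 1 + 7.84 × 4.903 = 39.4, so 40
- z2 = 1.28: 1 + 10.4976 × 4.903 = 52.5, so 53

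**7. What follows if z2 is corrected but n is not.** The design would drop to 36 per arm. At n = 30, √(35/4.903) − 1.96 = 0.71, which is power of about 76% before any loss.

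**8. Exclusive breastfeeding, 12 per arm in each country, k = 0.4.** The same power formula gives about 89% at n = 35, 88% at n = 30 and 85% at n = 24, so the effect there is small.

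**The case against.** A reader might infer that the trial can enrol at most 2880 infants and must miss 3360. The documents do not support that, for three reasons.

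- No recruitment period can be read. The time framework in section 9 is illegible in the copy at hand, and that cannot be held against the plan.
- Section 3.4 admits women from 6 months of pregnancy. A 12-month enrolment window would therefore take in roughly 12 + 3 = 15 months of births, or 30 × 15/12 = 37.5 per community and 96 × 37.5 = 3600 before losses. That is above 3360.
- Section 3.6 gives 1000 only as a typical average, and says that the unit varies between sites. Slightly larger communities would yield 35 births a year.

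It would also be too strong to say that 3360 does not follow from section 3.7: it is exactly 96 × 35. What fails is the step that produces 35.

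A further objection is that stated power is 80% and the corrected inputs still give 87%, so nothing changes. As arithmetic this stands. But the reserve comes from an inconsistency in the same table, 1.28 beside a beta of 0.20, and not from a planned allowance. Anyone who repairs that row while keeping n = 35 would remove the reserve.

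The objections therefore limit the size of the point. They do not remove the wrong product or the missing deduction.

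**Conclusion.** The point holds in a limited form. The births figure in section 3.6 is wrong on its own inputs: 30, not 35, so 35 is an overstatement of about 17%. Section 3.7 carries it unchanged into the sample size and all enrolment totals, treated as infants with a 3-month outcome and with no loss deducted. The 3360 is unsupported by the stated community size and birth rate, but not shown to be unreachable.

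The effect on diarrhoea power is modest while 48 communities per arm are kept: about 91% falls to 87% at n = 30 and to 81% at n = 24. The stated 80% fails only if more than about 22% of 30 births are not analysed. It would be wrong to conclude that the trial as designed is underpowered for its stated 80%.

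This rests on the plan's own p1, p2 and k, the unmatched formula above, equal cluster sizes, 30 births per community as the base, and assumed loss rates.

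**What to change.** - **Section 3.6:** change 35 to 30, or change the birth rate or the community size so that the three figures agree.
- **Section 3.7:** define n as infants analysed at 3 months, net of a stated loss allowance. The rate will be an assumption, so show power over a range such as n = 24 to 30.
- **Recruitment period:** state it next to n, even if section 9 already carries it, so that the expected births per community can be followed.
- **Totals:** restate 420, 840, 3360 and the power to match, and say whether the totals count infants enrolled or analysed.
- **Power value:** settle it in the same edit. At n = 30, 80% power (0.84) needs about 40 communities per arm, and 90% power (1.28) needs about 53. Do not reduce the number of communities on the strength of n = 35.

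The cost is protocol wording and a slightly less favourable number of children and power. If 80% is the intended power, 48 communities per arm remain enough down to 24 analysed infants per community, and none need be added. If 90% is intended, 48 is too few at n = 30.
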